#### Secondary outcomes

For binary outcomes, including the key secondary outcome of NEC, numbers and percentages will be provided. Risk ratios and 95% confidence intervals will be calculated using a mixed binomial, or Poisson model with a log link and robust variance estimator should the binomial model fail to converge. Risk differences will also be calculated using a mixed binomial model or Poisson model with an identity link. For continuous outcomes, mean and standard deviations or median and interquartile ranges will be presented. Mixed linear regression models will be applied, with mean differences and 95% confidence intervals presented, where model assumptions are satisfied. Skewed continuous outcomes will be analysed using quantile regression models, with median differences and 95% confidence intervals presented.

Secondary outcomes that are not tested will be presented using summary statistics. No tests of statistical significance will be performed, and no confidence intervals will be calculated between the randomised groups for the untested secondary outcomes.

### Who will be included in each analysis {27b}

#### Primary outcome

The primary analysis for the primary outcome of time to full feeds will be based on a modified intention-to-treat (ITT) approach; infants with outcome data available will be analysed in the groups to which they are assigned, regardless of deviation from the protocol or procedure received.

#### Secondary outcomes

For the key secondary outcome (non-inferiority outcome), the primary analysis will be based on a per-protocol population; infants with outcome data available, excluding those considered non-adherent before reaching full feeds, will be analysed in the groups to which they are assigned.

Non-adherence to trial intervention will be defined as the following occurring on two or more consecutive calendar days:

Babies allocated to the *N**o routine measurement of gastric residual*
*volumes* arm: Two or more gastric residual volume measurements. Where gastric residual volume measurements are undertaken during assessment for a clinical indication or concern, this will not be counted as non-adherence.

Babies allocated to the *Routine measurement of gastric residual volumes* arm: Less than three gastric residual volume measurements.

All other secondary outcomes will also be analysed using a modified ITT approach.

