#### Moderate to severe NEC

From the NNRD the incidence of significant NEC (requiring surgery, leading to death or recorded as part of the National Neonatal Audit Programme) is 3%. With a total sample size of 7040 and a control group event rate of 3%, the trial would have 92% power to detect a non-inferiority margin of 1.5% in the treatment risk difference, with a one-sided 2.5% significance level: non-inferiority can be claimed if the upper bound of the confidence interval of the treatment effect does not exceed 1.5%. These figures also allow for 10% crossover and 5% attrition. The inflation factor to account for the correlation in outcomes within multiple birth sets for NEC is 1% assuming a lower ICC of 0.05.

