#### Secondary analyses

A per-protocol analysis for the primary outcome and a modified ITT analysis for the key secondary outcome will be conducted applying the same statistical models as used for the primary analyses of these outcomes.

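### NEC non-inferiority rests on a per-protocol primary analysis, and the protocol does not say what is concluded if the modified ITT analysis disagrees

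*Protocol article*

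**What the plan says.** Three places in the protocol article bear on this.

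- **Who will be included in each analysis {27b}, Secondary outcomes.** For the key secondary outcome, "the primary analysis will be based on a per-protocol population; infants with outcome data available, excluding those considered non-adherent before reaching full feeds", are analysed as allocated. One run of two consecutive non-adherent days is enough for exclusion. In the no-routine arm such a day has two or more measurements, and those made for a clinical indication or concern do not count. In the routine arm it has fewer than three measurements, and no exemption is stated.
- **Methods for additional analyses {27d}, Secondary analyses.** "A per-protocol analysis for the primary outcome and a modified ITT analysis for the key secondary outcome will be conducted", with the same models as the primary analyses.
- **Sample size {19}, Moderate to severe NEC.** "non-inferiority can be claimed if the upper bound of the confidence interval of the treatment effect does not exceed 1.5" per cent. No population is named. The same paragraph gives the design figures: "With a total sample size of 7040 and a control group event rate of 3" per cent, "the trial would have 92% power to detect a non-inferiority margin of 1.5% in the treatment risk difference", "with a one-sided 2.5% significance level", and "These figures also allow for 10% crossover and 5% attrition".

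No section requires the two populations to agree or says what is concluded if they do not.

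**The concern.** Membership of the per-protocol set is settled after randomisation. Adherence is logged daily until full feeds, so an infant who takes longer has more days on which to meet the exclusion rule. Shortening that period is what the primary objective hopes the no-routine pathway will do, so allocation may change the window. The triggers differ by arm, the exemption is written for one arm only, and the sample size section expects crossover in the no-routine group. Equal exclusion in the two arms cannot be presumed.

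If infants who are slow to reach full feeds also carry more NEC risk, exclusion removes NEC cases selectively. Blinded adjudication protects how NEC is classified, but not who enters the set, because treating staff and those recording outcomes are unblinded. At stake is the safety half of the trial's conclusion: non-inferiority could be claimed on the per-protocol bound while the randomised comparison exceeds 1.5 points.

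**Working it through.** **1. The plan's own figure.** Inputs from the sample size section: 3520 per arm, 5% attrition, design effect 1.01, 10% crossover, 3% NEC in both arms, margin 1.5 points, one-sided 2.5%.

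- Modified ITT effective n = 3520 × 0.95 / 1.01 = 3311 per arm. Per-protocol n = 3311 × 0.90 = 2980.
- Power = Φ(0.015 / √(2 × 0.03 × 0.97 / n) − 1.96).
- n = 2980 gives 92.4%, which matches the stated 92%. n = 3311 gives 94.7%.

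The stated power is not in dispute.

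**2. Exclusion by length of the window.** Assumptions: time to full feeds T is lognormal with the protocol's mean 9.4 and SD 10.8 days, and the daily chance h of meeting the rule is constant, so P(excluded | T) = 1 − exp(−hT). For 10% excluded overall, h is about 0.012 per day. Exclusion is then 5.8% at day 5, 11.3% at day 10, 21.3% at day 20 and 38.0% at day 40. Only about 2% of infants lie beyond day 40. Using T from birth slightly overstates the window, which opens at randomisation.

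**3. Chance of a false claim.** True rates are 3% (routine) and 4.5% (no-routine), exactly at the margin. NEC risk is assumed proportional to √T or to T. In each arm the rate among retained infants is the true rate times f, where f = E[w·exp(−hT)] / E[exp(−hT)] and w is the relative risk at T, scaled to mean 1. Then P(claim) = Φ((0.015 − difference) / SE − 1.96), with n = 3311 × (1 − share excluded) in each arm.

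Worked line, 10% excluded from the no-routine arm only, risk proportional to T: f = 0.884, so the no-routine rate is 4.5% × 0.884 = 3.98%. The difference is 0.98 points and the SE 0.465 points. Φ(0.522 / 0.465 − 1.96) = 20.1%.

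| Excluded, no-routine / routine | False claim (√T to T) | Per-protocol power at equal 3% rates |
|---|---|---|
| 10% / 0% | 6.8–20.1% | 97–99% |
| 15% / 5% | 7.5–22.7% | 97–99% |
| 10% / 10% | 3.5–5.7% | 94–95% |
| 5% / 10% | 2.1–1.7% | 92–89% |
| 5% / 15% | 1.5–0.7% | 88–81% |
| Any split, NEC unrelated to T | 2.5% | 92–94% |

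Equal shares still raise the error a little, because removing higher-risk infants lowers both rates and shrinks an absolute difference.

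**4. Two verdicts from one dataset.** Take 3344 per arm (3520 × 0.95) and 100 NEC cases in the routine arm. Modified ITT meets the limit with at most 121 no-routine cases (upper bound 1.489%; 122 gives 1.521%). Now exclude 10% of the no-routine arm only, with excluded infants at twice the NEC risk of those kept (assumption). The per-protocol bound is still 1.482% with 132 randomised cases, 108 of them retained, while the modified ITT bound is 1.84%. At equal risk there is no such gap.

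**5. Modified ITT alone.** If 10% crossover dilutes a true 1.5 points to 1.35, modified ITT claims non-inferiority with probability Φ(0.15 / 0.462 − 1.96), about 5%.

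**The case against.** A per-protocol primary analysis is a recognised choice for non-inferiority, because crossover pulls an ITT comparison towards no difference. Step 5 shows that this matters here. That stands, and it is why the per-protocol analysis should stay.

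A reader might infer that modified ITT will be ignored. The documents do not support that: "a modified ITT analysis for the key secondary outcome will be conducted" with the same models, so a disagreement would be visible. What is missing is its place in the decision. The SAP is not shown and may supply it, but the protocol already fixes the per-protocol set as primary and would have to agree.

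A reader might also infer that the rule is biased towards a false claim of safety, with an error near 20%. That is not established either. The protocol gives no exclusion rate by arm and no NEC risk by time to full feeds. Its 10% crossover is described for the no-routine arm, which points towards the unsafe direction. The clinical-indication exemption keeps in that arm infants measured because of gut signs and could shift exclusions to the routine arm, where the error falls below nominal and power is lost instead.

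**Conclusion.** The point holds as a gap in the decision rule. The deciding population is formed after randomisation, by rules that differ between arms, and the protocol does not say what is concluded if the randomised comparison disagrees. The direction of any bias is unknown.

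Across the splits shown, the false-claim rate runs from 0.7% to 22.7% against a nominal 2.5%. That range rests on assumed exclusion shares, a lognormal time with constant daily hazard, and an assumed rise of NEC risk with time to full feeds. Without that rise there is no inflation. The structural point is firm; the magnitudes are illustrative. Because NEC is the key safety conclusion and the rule can be settled before results are known, it should be changed.

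**What to change.** Keep the per-protocol analysis. State in the NEC sample size paragraph, under {27b} and under {27d}, and identically in the SAP: non-inferiority is claimed only if the upper limit of the 95% confidence interval for the risk difference does not exceed 1.5 points in both the per-protocol and the modified ITT populations; if they disagree, it is not claimed.

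Cost in power, with no extra infants:

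- If exclusion is unrelated to NEC risk, joint power is about 91.7% (bivariate normal, marginals 92.4% and 94.7%, correlation √0.9 = 0.95), against 92.4% for per-protocol alone: about 0.7 point.
- Where selective exclusion lifts per-protocol power to 97–99%, modified ITT caps joint power at about 95%. That gives up 2 to 4 points of inflated power, and the cap is still above the stated 92%.
- Where exclusions fall mainly on the routine arm, per-protocol power of 81–88% is the limit. That loss already exists under the present rule.

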### Explanation for the choice of comparators {9b}

Two pathways of care are being compared:No routine measurement of gastric residual volumesRoutine, at least 6-hourly, measurement of gastric residual volumes

Both pathways represent standard clinical practice in different neonatal units in the UK and Australia; they are based upon UK and international practice [2] and a consensus meeting [7] which involved parents, neonatologists, neonatal nurses, dieticians and trial methodologists.

The allocated pathway of care will be followed:For as long as routine gastric residual volume measurement is standard local practice,Until gastric feeding tubes are no longer required,The infant is discharged home, orThe infant reaches 44 + 0 gestational weeks + days.

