### Criteria for discontinuing or modifying allocated intervention/comparator {15b}

Where an infant develops a condition for which gastric residual measurement is clinically indicated—for example, suspected NEC or gastrointestinal obstruction, or following abdominal surgery—such gastric residual measurement is no longer ‘routine’ so should be undertaken as clinically indicated in both trial arms. When gastric residual measurement is no longer clinically indicated, the infant should resume their allocated care pathway if this is considered clinically appropriate.

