### Participant timeline {18}

**Table Tabc:** 

	**Period**						
	**Enrolment**		**Post-randomisation**				**Close-out**
**Timepoint**	**After birth**	**After eligibility confirmed**	**Day 1**	**Day 2**	**Day 3**	**etc**	**Discharge from neonatal unit or 44 + 0 gestational weeks + days**
Enrolment							
Eligibility screen	X						
Opt-out consent	X						
Randomisation		X					
Baseline data		X					
Intervention/comparator							
*Routine* or *no routine* measurement of gastric residual volumes			X	X	X	X	
Assessments							
Daily feeding log			X	X	X	X^a^	
Late-onset infection and gut signs						X^b^	
Data at discharge or **44 + 0 gestational weeks + days**							
Clinical data^c^							X^d^

^a^Daily feeding logs until day 14, and then until the infant achieves full enteral feeds (at least 145 ml/kg/day where this is considered full enteral feeds, or where breastfeeding and any additional milk is considered equivalent to full enteral feeds) for 3 consecutive days, or reaches 44 + 0 gestational weeks + days

^b^Each episode of microbiologically confirmed or clinically suspected late-onset invasive infection, or if an infant has received at least 5 days of treatment for gut signs, if they are transferred with gut signs, or if they have died from gut signs, should be reported throughout the treatment period until hospital discharge

^c^Clinical data is collected via the electronic case report form or from routinely recorded clinical data where applicable

^d^If infant is withdrawn from the trial and parent/carer has asked for no further data collection, the transfer/discharge form can be completed at the time of withdrawal for data up until point of withdrawal

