### Plans to promote participant retention and complete follow-up {25b}

The Project Management Group (PMG) will remotely monitor the completeness of study documentation and maintain regular contact with all sites to ensure the accuracy and completeness of all study documentation during the infants’ participation in the study. For infants who discontinue participation or where there is a deviation from protocol after the point of randomisation, sites will be asked to record the reasons for this and to continue data collection, where possible, so they can be included in the analysis of outcomes, according to the intention to treat analysis principle.

To support participant retention, several strategies will be implemented throughout the trial. All recruiting sites will receive training at setup, with ongoing support provided via the study website and through direct contact with the trial coordinating team as needed. The Parent Information Sheet (PIS) will be translated into seventeen languages other than English to help make the trial information accessible to families from diverse backgrounds. If an infant is discontinued from the allocated trial pathway but remains in the trial, data collection will continue. If an infant withdraws from the trial completely, data collected up to the point of withdrawal will be used for analysis. Monthly reports on missing data and outstanding CRFs will be shared with sites.

Communication between recruiting sites and Continuing Care Sites (CCSs) will be actively facilitated by the trial coordinating team at the National Perinatal Epidemiology Unit (NPEU) CTU, to support continued data collection following any infant transfers, including to non-CCSs. To maintain engagement, the trial will include structured retention and communication strategies, including staff recognition and family-facing materials. Monthly informal meetings with the coordinating team will provide sites with an opportunity to ask questions, exchange ideas, share key learnings and troubleshoot issues collaboratively.

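### The non-adherence rule for the primary NEC analysis exempts protocol-directed care in the no-routine arm only, so compliant infants can be excluded from the routine arm alone

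*Protocol article*

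**What the plan says.** All references are to the protocol article.

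- **Who will be included in each analysis {27b}, Secondary outcomes.** The primary analysis of NEC uses a per-protocol population, "excluding those considered non-adherent before reaching full feeds". Non-adherence must occur on at least two consecutive calendar days. In the no-routine arm it means two or more measurements, with an exemption: "Where gastric residual volume measurements are undertaken during assessment for a clinical indication or concern, this will not be counted as non-adherence". In the routine arm the whole rule is "Less than three gastric residual volume measurements".
- **Criteria for discontinuing or modifying allocated intervention/comparator {15b}.** With suspected NEC, obstruction or after abdominal surgery, measurement stops being routine and "should be undertaken as clinically indicated in both trial arms". The infant returns to the allocated pathway afterwards if that is clinically appropriate.
- **Explanation for the choice of comparators {9b}.** The pathway is followed "For as long as routine gastric residual volume measurement is standard local practice", and until a gastric tube is no longer needed, discharge home or 44+0 weeks. The same section says "Both pathways represent standard clinical practice in different neonatal units in the UK and Australia".
- **Strategies to improve adherence {15c}.** Daily measurement counts are recorded until the primary outcome is reached.
- **Secondary analyses, under {27d}.** A modified ITT analysis of NEC is planned as a secondary analysis.

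**The concern.** The rule in {27b} recognises that clinical need can override the allocated schedule, but it protects only one arm from the consequence. During an episode under {15b} no minimum frequency applies. After the tube is no longer required, or once routine measurement is no longer local practice, {9b} asks for no routine measurement at all. In each case a routine-arm infant with fewer than three measurements on two consecutive days has followed the protocol and still meets the exclusion rule. A no-routine infant in the same position is kept, because low counts cannot breach that arm's rule and clinically indicated counts are set aside.

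This affects the primary analysis of the key safety outcome. The exclusions arise after randomisation and, through {15b}, can be triggered by suspicion of the very outcome being compared. The arms stay comparable only if the infants lost have the same NEC risk as the rest of the routine arm.

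**Working it through.** **1. The sections side by side**

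| Situation before full feeds | What the protocol directs | Routine arm under {27b} | No-routine arm under {27b} |
|---|---|---|---|
| Suspected NEC, obstruction, after abdominal surgery ({15b}) | Measure as clinically indicated | Excluded if fewer than 3 a day for 2 days | Kept, by exemption |
| Tube no longer required ({9b}) | Pathway over | Excluded if 2 such days fall before full feeds | Kept |
| Routine measurement not local practice, for example after transfer ({9b}) | Pathway over | Excluded after 2 such days | Kept |

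These situations can arise within the adherence window:
- Participant timeline {18} asks for a report "if an infant has received at least 5 days of treatment for gut signs, if they are transferred with gut signs", so episodes longer than two days are foreseen.
- Full feeds may be met by breastfeeding with any additional milk, so a tube can be out before the three qualifying days are complete.
- Section {25b} provides for contact between sites "to support continued data collection following any infant transfers, including to non-CCSs".

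**2. The plan's own NEC power**

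Inputs from Sample size {19}: 3520 per arm, control rate 3%, margin 1.5 points, one-sided 2.5%, 5% attrition, 1% clustering inflation, 10% crossover.

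n = 3520 × 0.95 / 1.01 × 0.90 = 2980 per arm

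SE = √(2 × 0.03 × 0.97 / 2980) = 0.00442

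Power = Φ(0.015 / 0.00442 − 1.96) = Φ(1.434) = 92.4%, against 92% stated. The stated figure is sound, and the point here is the population definition.

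**3. Illustration of size**

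Two inputs are not in the document and are assumed: m, the share of the routine arm excluded for want of an exemption, and r, the NEC rate among those infants. The illustration takes n = 3520 × 0.95 = 3344 per arm, a full-arm rate of 3% in the routine arm, and no exclusions from the no-routine arm.

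- Retained routine-arm rate: q = (0.03 − m·r) / (1 − m)
- SE = √(q(1−q) / (n(1−m)) + p₁(1−p₁) / n), where p₁ is the no-routine rate
- P(claim) = Φ((0.015 − (p₁ − q)) / SE − 1.96)
- False claim uses p₁ = 4.5%; power uses p₁ = 3%.

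Example, m = 10% and r = 1.5%: q = (0.03 − 0.0015) / 0.9 = 3.17%. With p₁ = 4.5%, SE = 0.00480 and P(claim) = 5.3%.

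| r | m | q | False claim | Power |
|---|---|---|---|---|
| any | 0 | 3.00% | 2.5% | 94.9% |
| 1.5% | 2% | 3.03% | 2.9% | 95.4% |
| 1.5% | 5% | 3.08% | 3.7% | 96.0% |
| 1.5% | 10% | 3.17% | 5.3% | 97.0% |
| 3% | 10% | 3.00% | 2.5% | 93.8% |
| 6% | 2% | 2.94% | 1.8% | 93.2% |
| 6% | 5% | 2.84% | 1.1% | 89.6% |
| 6% | 10% | 2.67% | 0.4% | 80.0% |

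If only NEC cases were lost, 5 or 10 of about 100 (3344 × 0.03), power would fall to 90.7% or 84.3%.

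**4. Keeping infants who are no longer measured**

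Suppose a share m of the routine arm stops being measured, is kept, and carries the full no-routine risk of 4.5%, which is an upper bound. Then q = 0.03(1 − m) + 0.045m. At m = 5%, q = 3.075% and the false-claim chance is 3.6%. At m = 10%, q = 3.15% and it is 5.1%. That is about the same as the inflation from excluding low-risk infants in step 3.

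**The case against.** The strongest reply is that the exemption is one-sided for a good reason. Section {15b} concerns conditions in which measurement is indicated, so it tends to add measurements, and added measurements threaten only the no-routine arm's upper limit. A reader might infer that {15b} tells staff to stop measuring. It does not. Nothing in the document says that counts fall below three a day in such episodes, and the five-day criterion in {18} is a reporting threshold that says nothing about frequency. This limits how often the route operates. It does not remove the conflict, because {15b} sets no minimum and {27b} does.

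The {9b} route is also narrow. Only days before full feeds count, and infants this immature seldom do without a tube by then. Transfers are mentioned in {25b} for data collection only, with no frequency given.

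A third objection stands in full. A routine-arm infant who moves to a non-measuring unit no longer receives the comparator, and keeping that infant dilutes the contrast (step 4). Declaring all such infants adherent would be a choice of estimand and not a plain correction.

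Finally, day-level adherence rules are often left to the SAP. Here, though, the article fixes a numerical rule for each arm and grants an exemption to one. That is a stated rule in conflict with other sections, and a SAP that follows it inherits the conflict.

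**Conclusion.** The point holds as an inconsistency in a stated rule. Read literally, {27b} can exclude protocol-compliant infants from the routine arm alone in the primary NEC analysis. It should be corrected before analysis.

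Its size is not known. A reader might infer that the rule biases the trial towards a non-inferiority claim, or that the distortion is substantial. The document supports neither. Losing low-risk infants favours the claim and losing infants with suspected NEC works against it. Infants lost at the arm's own 3% rate cause no bias. With m at 2% and r between 1.5% and 6%, the false-claim chance stays at 1.8% to 2.9% and power at 93% to 95%. The larger figures need m of 5% to 10%, for which the document gives no evidence. They also assume no exclusions from the no-routine arm, although {19} anticipates crossover there. The modified ITT analysis would reveal a material discrepancy, but being secondary it does not correct the primary result.

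**What to change.** Amend {27b}, or state in the SAP, that in both arms the following do not count towards non-adherence:

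- days of clinically indicated management under {15b};
- days after a gastric tube is no longer required.

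Report per-protocol exclusions by arm with reasons. For infants who transfer to a non-measuring unit, or who reach a site's own stopping point for routine measurement, run the NEC analysis with them kept and with them excluded, without fixing their status as adherent.

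The cost is a sentence or two of text. Daily counts are already collected. Days under {15b} in the routine arm need a flag, or a proxy from the gut-sign and feeds-withheld records; the feeds-withheld outcomes run only to 14 days from randomisation. The sensitivity analysis needs each site's measurement practice, including that of receiving units. The drawback is that genuine non-adherence during a clinical episode would no longer lead to exclusion.
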